### Randomization

Families will be stratified by study centre and diagnosis. Random number sequences will be generated in a 1:1 ratio using statistical software by an independent statistician and written into the electronic data collection (EDC) software developed specifically for this study. The random number sequence will be generated by third-party engineers commissioned to develop the EDC software and cannot be accessed by the research team. Participants will be allocated automatically within the software after completing screening assessments and enrolment is confirmed.

This study will not use masking. Because this study employs wait list control, participants and therapists will be aware of allocation status. Masking of researchers will also be difficult as in most study sites, researchers share office space with therapists, therefore they will likely see participants coming in for sessions.

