### Sample size calculations

Sample size was calculated using SDQ as the primary outcome. Data from multiple countries (https://www.sdqinfo.org/g0.html) show that the population standard deviation of SDQ is roughly 5 points. Considering an SDQ difference of 3 points to be a clinically significant difference, at α = 0.05 and β = 0.9 levels, assuming a two-sided hypothesis and using 1:1 ratio of random allocation, the sample size needed for analysis is 120. As families with schizophrenia and bipolar disorder will be analysed separately, assuming a 40% dropout rate, 200 subjects will be needed for each diagnostic category. Therefore, 200 families with schizophrenia, and 200 with bipolar disorder will be enrolled.

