### Statistical analysis

Baseline categorical variables will be summarized as proportion of subjects with the count divided by the total number of evaluated subjects. Baseline continuous variables will be summarized as mean with standard deviation in case of normal distribution and as median with interquartile range in case of non-normal distribution. Efficacy will be assessed in the intention-to-treat population. Missing data will be imputed using the last observation carried forward method. Outcome variables will be differences between pre- and post-test scores at 50 days and 200 days.

Primary outcomes will be compared using t-tests if results conform to a normal distribution and nonparametric tests if they do not. Multivariate generalized linear regression models will be performed with outcome variables as the dependent variable, group allocation as the independent variable, and baseline variables as covariates to account for potential confounding. Data will be analysed as a whole and also separately in the two diagnosis groups. Further subgroups will be explored using interaction tests in the multivariate regression models. Potential subgroup identifiers include but are not limited to child mental health at baseline, parental disease severity, family socioeconomic status and child age. All inferences will be made at a significance level of α = 0.05.

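### The primary outcomes are tied to an unadjusted change-score test picked by a normality check; one prespecified baseline-adjusted model would be more precise and would keep the quantity tested fixed

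*Protocol article*

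**What the plan says.** All of this is in the protocol article.

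- **Outcome variable** (Statistical analysis): "Outcome variables will be differences between pre- and post-test scores at 50 days and 200 days".
- **Test named for the primary outcomes** (same section): "Primary outcomes will be compared using t-tests if results conform to a normal distribution and nonparametric tests if they do not". No covariate or stratum is attached to it, and no criterion for normality is given.
- **Second analysis** (next sentence): "Multivariate generalized linear regression models will be performed with outcome variables as the dependent variable, group allocation as the independent variable", with "baseline variables as covariates to account for potential confounding". The text does not rank this model against the t-test or rank test.
- **Populations** (same section): "Data will be analysed as a whole and also separately in the two diagnosis groups". Efficacy is assessed by intention to treat, with missing values filled by last observation carried forward (LOCF).
- **Randomisation** (Randomization): "Families will be stratified by study centre and diagnosis". The Setting section gives 10 centres.
- **Sizing** (Sample size calculations): the "population standard deviation of SDQ is roughly 5 points", and "Considering an SDQ difference of 3 points to be a clinically significant difference". This gives 120 analysable families per diagnosis, raised to 200 for 40% dropout.

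**The concern.** Three features of the named primary test work against the trial.

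1. A change score fixes the slope on baseline at 1. ANCOVA estimates that slope and has smaller variance whenever r is below 1. The precision is given up although the baseline score is already collected.
2. The test is settled only after the distribution of the trial data has been inspected. The two branches address different quantities: the t-test addresses a difference in means, which is what the 3-point sizing figure describes, and a rank test does not. LOCF feeds into this check, because a family lost before day 50 contributes a change of exactly zero.
3. A t-test or rank test and a regression are applied to the same outcomes, and the text does not say which one decides. In an open-label trial that counts success on either of two scales, the deciding analysis should be fixed beforehand. The reason given for adjustment is confounding; under randomisation the stronger reasons are precision and agreement with the stratified design.

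**Working it through.** **The plan's own figure.** Inputs: difference 3, SD 5, two-sided alpha 0.05, 1:1 allocation, and the printed β = 0.9 read as power 0.90. The normal approximation gives 59 per arm, 118 in total. The t-test calculation gives 59.35, rounded up to 60 per arm, 120 in total. Then 120 / (1 − 0.40) = 200. The stated figures reproduce.

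**What that figure assumes about the analysis.** The SD of 5 describes the score, not its change. With equal SDs at both visits and correlation r (an assumption, shown over a range):

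- SD of change = 5·√(2(1 − r))
- residual SD under ANCOVA = 5·√(1 − r²)
- variance ratio, ANCOVA to change = (1 − r²) / (2(1 − r)) = (1 + r)/2

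The SD of change equals the planned 5 only at r = 0.5. Below that it is larger.

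**Precision and power**, difference 3. Power is for 60 per arm by the t distribution; total N per diagnosis is for 90% power by the normal approximation.

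| r | SD change | SD ANCOVA | variance ratio | power, change | power, ANCOVA | N, change | N, ANCOVA |
|---|---|---|---|---|---|---|---|
| 0.3 | 5.92 | 4.77 | 0.65 | 0.787 | 0.927 | 164 | 108 |
| 0.4 | 5.48 | 4.58 | 0.70 | 0.845 | 0.945 | 142 | 100 |
| 0.5 | 5.00 | 4.33 | 0.75 | 0.903 | 0.964 | 118 | 88 |
| 0.6 | 4.47 | 4.00 | 0.80 | 0.954 | 0.983 | 94 | 76 |
| 0.7 | 3.87 | 3.57 | 0.85 | 0.988 | 0.995 | 72 | 60 |
| 0.8 | 3.16 | 3.00 | 0.90 | 0.999 | 1.000 | 48 | 44 |

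**The normality switch under LOCF.** Simulated day-200 change: 100 per arm, SD 5, r = 0.5, a 3-point effect in families observed after baseline, and 40% dropout split between before day 50 (early) and after it (late). Shapiro-Wilk at 5% stands in for the unnamed check and counts as failed if either arm is rejected.

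| early / late dropout | check fails | t-test power | rank-test power |
|---|---|---|---|
| 40% / 0% | 100% | about 0.90 | about 0.83 |
| 20% / 20% | over 90% | 0.96 | 0.95 |
| 10% / 30% | about a third | 0.98 | 0.97 |
| 0% / 40% | about 10% | 0.98 | 0.98 |

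With all dropout early, ANCOVA has power of about 0.94 at r = 0.5. For other r, still with all dropout early, rank test, t-test and ANCOVA give 0.69, 0.77 and 0.86 at r = 0.3, and 0.96, 0.98 and 0.99 at r = 0.7.

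**The strata.** Simulation of 10 centres with 12 families each, 6:6 within centre, difference 3, 20,000 replicates, assumed centre ICC:

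- ICC 0.05: type I error 4.6% without centre and 5.1% with it; power 91.2% and 91.9%.
- ICC 0.10: type I error 4.0% and 5.0%; power 91.4% and 92.8%.

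Leaving centre out makes the test slightly conservative and costs about 1 point of power.

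**The case against.** The strongest reply is that the better model is almost there already. Regressing the change (Y − B) on arm and baseline B gives the same arm coefficient as regressing Y on arm and B; only the coefficient on B shifts by 1. If the baseline score is among the planned covariates, the regression is ANCOVA. The exact covariate list may well be in an analysis plan that is not shown, so its absence here is not counted against the protocol. This stands. It does not settle the point, because the article attaches the primary outcomes by name to the unadjusted test and does not say that the regression decides.

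Several stronger readings are tempting but not supported:

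- **That baseline is ignored.** It is not: a change score uses it, with a fixed slope.
- **That the trial is underpowered.** With 60 per arm analysed, the change-score t-test falls below 90% only for r under 0.5, and the document gives no r. At r of 0.5 or more the loss is inefficiency only.
- **That LOCF makes the rank test inevitable.** Only families lost before day 50 have a change of zero; later losses carry their day-50 score to day 200. The article gives no timing for the 40%, and names no normality test.
- **That analysts may freely choose between t-test and rank test.** The switch itself is prespecified; only its criterion is open.
- **That omitting the strata invalidates the test.** The effect is small and conservative, and diagnosis is already handled in the separate analyses on which the trial is sized.

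**Conclusion.** The point holds as one of efficiency and clarity, and it should be changed. The test named for the primary outcomes has a variance that ANCOVA would cut by 35% at r = 0.3, 25% at r = 0.5, 15% at r = 0.7 and 10% at r = 0.8. In power at 60 per arm that is a gain of about 14 points, 6 points, under 1 point and practically nothing. These figures rest on an assumed r, equal SDs at both visits, and the plan's own 3 points and SD of 5.

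The normality switch is a separate weakness. It lets the data decide whether the trial tests the quantity on which it was sized. How often it would trigger depends on when families drop out. Its power cost is clear only when dropout is mostly early, at about 0.83 against 0.90 for r = 0.5, and is about 1 point or less in the mixed and late scenarios. The case for including centre is consistency with the randomisation rather than power.

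**What to change.** Name one primary analysis and apply it whatever the distribution: a linear model of the follow-up score on arm, with the baseline score of the same scale, centre and, in the pooled analysis, diagnosis as covariates. Report the adjusted mean difference with its 95% confidence interval. Remove the normality condition and keep the rank test as a sensitivity analysis. Give precision and the stratified design as the reasons for adjustment, in place of confounding.

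The cost is a change of wording in the protocol or analysis plan, made before data are exported for analysis. Baseline scores, centre and diagnosis are already collected, no extra families are needed, and the planned 200 per diagnosis can stay as it is.

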### Data management and security

An electronic data collection software was developed specifically for this study. Researchers and therapists will have password protected accounts with different access permissions according to their role. Only the trial management group can view data from all centres. Participants will be provided one-time links to online questionnaires for their own record. The trial management group will monitor the dataset weekly for missing data, outliers, protocol deviation and other potential issues. Dropouts will be directly recorded by site staff through the EDC software. After completion of the study, de-identified data will be exported from the software by the primary statistician and stored on a password protected computer. No interim analyses are planned.

### Monitoring and auditing

A trial management group led by LG has been set up to oversee study implementation through weekly meetings and in person or online communications as needed. A biweekly video conference will be held with researchers and therapists from all study sites to communicate study progress and discuss potential issues. Members of the trial management group will visit each site periodically to audit treatment fidelity and data collection.

### Safety assessment

Adverse events will be monitored and recorded throughout the study. Few adverse events are anticipated as the intervention is clinical therapy. In case of distress, agitation or risk to self or others, subjects will be referred to psychiatric care.

### Dissemination policy

Results of this trial will be published in a peer-reviewed journal. Study findings will be disseminated through international and domestic academic meetings. A simplified version of the results will be published in our study team’s WeChat public account titled “CAFF花园” which targets COPMI, their families, mental health professionals and other people interested in the mental health of COPMI.

## Discussion

To our knowledge, this study is the first to assess LTC in families with parental schizophrenia and is the second in families with parental bipolar disorder worldwide. LTC is a brief and simple intervention that has potential to improve mental health and prevent mental disorders in high-risk children. However, LTC has only been tested in limited settings. Previous evidence regarding LTC focuses on families with parental depression [10, 24, 28]. Families with severe parental mental disorders face significantly greater parenting challenges compared to families with parental depression. Parents with severe mental disorders may exhibit violent behaviours, be absent due to hospitalization, or have poorer overall functioning. Severe mental disorders are also more stigmatized than depression [17, 22]. Therefore, families with severe parental mental disorders are in greater need of parenting support. Anecdotal reports of clinicians’ implementation of LTC in families with severe parental mental disorders have been positive [1], however there is a lack of quantitative evidence regarding its efficacy in this population. Therefore, our study will provide valuable information for future clinical practice in families with severe mental disorders worldwide.

Previous research has found that both mothers and fathers with mental illness in China have parenting concerns related to their mental illness [6, 7], however there are currently no evidence-based family focused therapies to address this issue in China. If positive, results from this study will provide much needed treatment option in Chinese speaking families with parental mental illness.

The primary limitation of this study is the inability to blind participants, therapists and research workers to randomization status, which may lead to overestimation of intervention effects because of observer bias. Another limitation is that the therapists participating in this study have no previous experience delivering LTC as this intervention was introduced to China only recently by our study team, which may result in poorer efficacy compared to experienced therapists. Our team will conduct detailed training and supervision throughout the study to ensure fidelity and congruency across different sites.

The results of this study will increase evidence for using LTC in prevention and early intervention of mental disorders in COPMI. If results are positive, further cost effectiveness analyses will be conducted which may provide a basis for widespread implementation of LTC in families with schizophrenia or bipolar disorder in China.

## Data Availability

No datasets were generated or analysed during the current study.
